#### Secondary outcomes.

Secondary outcomes include:

species-specific incidence density of hospital-acquired ESBL-producing *Escherichia coli*;species-specific incidence density of hospital-acquired ESBL-producing Enterobacterales other than *E. coli*.

#### Exploratory outcomes.

Exploratory outcomes include hand hygiene compliance rates, compliance with personal protective equipment donning and doffing procedures, and patient-reported anxiety and depression assessed using the Hospital Anxiety and Depression (HAD) scale or a Likert scale when applicable.

### Randomization

The order of implementation of the two study periods (CP and SP) is randomly assigned at the site level. Each participating site is allocated to one of two possible sequences (CP followed by SP, or SP followed by CP) using simple randomization with a block size of two, to ensure different initial sequences across sites.

The randomization sequence is generated by the methodologist of the Clinical Research Support Platform at the Metz–Thionville Regional Hospital Center and stored in a secure electronic file. The allocation sequence is communicated to the investigators prior to study initiation.

The organization of the intervention according to study site and randomized period order is illustrated in Figure 3.

**Fig 3 pone.0353783.g003:**
[figure not shown]
Flowchart of study procedures.

#### Blinding organization of surveillance screening results.

Rectal screening for ESBL-E carriage performed at admission and discharge is conducted exclusively for research purposes. Results of these surveillance screenings are not communicated to ward staff during either study period. This approach is intended to prevent behavioral changes that could bias comparisons between infection prevention policies.

Specifically, during CP periods, disclosure of surveillance results could lead to implementation of CP beyond routine practice, whereas during SP periods, knowledge of colonization status could increase vigilance and artificially reduce cross-transmission.

Surveillance screening results are therefore accessible only to the microbiology laboratory, the clinical research support platform, and the IPC team. Results of rectal swabs are not recorded in the electronic medical record and are documented solely in the study case report form (CRF).

Importantly, results of routine clinical microbiological cultures (e.g., urine or blood cultures performed for suspected infection) are communicated to clinical teams as usual and guide antimicrobial prescribing and patient management. Only surveillance rectal screening results performed for research purposes are concealed from ward staff.

Ward staff and patients cannot be blinded to the IPC policy implemented during each period. However, patients are not informed of surveillance screening results, as these are not used for clinical decision-making.

Unblinding of surveillance results occurs only in the event of detection of emerging extensively drug-resistant bacteria (eXDR), in accordance with national “search and isolate” recommendations. In such cases, CP are immediately implemented as required for patient safety.

### Sample size

Based on a study conducted in an acute geriatric unit at a Belgian teaching hospital [31], we assumed an incidence density of 1 hospital-acquired ESBL-E acquisition per 1,000 patient-days during CP periods. The non-inferiority margin was set at 1 additional acquisition per 1,000 patient-days, based on a previous prospective non-inferiority study conducted in the intensive care unit of the same hospital institution evaluating discontinuation of contact precautions for MRSA and ESBL-E [29]. This threshold was considered clinically acceptable for the present pragmatic infection prevention study. Using a one-sided alpha of 5% and 80% power, a total of 6,178 patient-days were required.

After accounting for clustering using an intra-cluster correlation coefficient of 0.003 [32] and a design effect of 1.48 [33], the required sample size increased to 9,130 patient-days.

Based on an average length of stay exceeding four days, a total of 954 patients will be included to achieve the required number of patient-days, accounting for an anticipated 15% exclusion rate.

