## Introduction

### Background and rationale

Multidrug-resistant Gram-negative bacteria (MDR-GNB) pose a major global health challenge in the 21st century [1,2]. Since the early 2000s, the prevalence of third-generation cephalosporin–resistant Enterobacterales has steadily increased worldwide. Extended-spectrum β-lactamase–producing Enterobacterales (ESBL-E) are a major contributor to this rise [3], with numerous outbreaks reported in healthcare settings, particularly in intensive care units (ICU) and long-term care wards, leading to increased morbidity, mortality, and healthcare costs [4,5].

Initially, Klebsiella pneumoniae was the most frequently isolated ESBL-E species, but more recent epidemiological data indicate a growing burden of ESBL-producing Escherichia coli, especially in community settings [6]. In France, national surveillance data have shown a continuous increase in ESBL-E incidence, with incidence density rates now three to four times higher than those observed for methicillin-resistant Staphylococcus aureus (MRSA) [7].

Advanced age is a well-established risk factor for infection [8], largely due to immunosenescence and the high prevalence of chronic comorbidities [9–11]. A multicenter prevalence study conducted in eight French hospitals identified hospitalization in geriatric wards as a significant risk factor for ESBL-E carriage, with 28.2% of geriatric inpatients colonized [12]. Prolonged care and frequent exposure to biological fluids in geriatric settings further increase the risk of cross-transmission.

Elderly inpatients therefore present multiple risk factors for colonization with multidrug-resistant organisms (MDRO), including antibiotic exposure, colonization pressure, and organizational factors such as workload and care density. Several studies have demonstrated associations between staffing constraints, increased workload, and healthcare-associated infection risk [13,14]. Despite this, geriatric wards remain relatively understudied as potential reservoirs of ESBL-E.

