### Outcomes

#### Primary outcome.

The primary outcome is the incidence density of hospital-acquired ESBL-E per 1,000 patient-days, defined as ESBL-E detection at discharge following a negative admission screening.

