### Statistical methods

Patient characteristics will be summarized using means (± standard deviation) or medians (interquartile range) for continuous variables and counts (percentages) for categorical variables.

A non-inferiority analysis will be conducted to evaluate whether standard precautions are non-inferior to contact precautions with respect to the incidence density (per 1,000 patient-days) of hospital-acquired ESBL-E. The non-inferiority margin is set at Δ = 1 additional acquisition per 1,000 patient-days.

The primary analysis will compare ESBL-E acquisition incidence rates between SP and CP periods using a count regression model (Poisson or negative binomial in case of overdispersion), with log(patient-days) included as an offset. Models will include fixed effects for intervention (SP vs CP), calendar period or season, and period order. Additional adjusted analyses will include systemic antibiotic exposure during hospitalization as a covariate to account for antimicrobial pressure as a potential confounding factor. Marginal incidence rate differences (SP − CP, per 1,000 patient-days) and their one-sided 95% confidence intervals will be derived from the fitted models. Non-inferiority will be concluded if the upper bound of the one-sided 95% confidence interval is below the predefined margin.

All analyses will be performed using SAS version 9.3 (SAS Institute, Cary, NC, USA).

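### Neither the patient-day target nor the offset is limited to patients with a negative admission screen, and the mean stay behind the 954 patients is not given

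*Protocol article*

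**What the plan says.** All references are to the protocol article.

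- **Primary outcome:** an acquisition is "defined as ESBL-E detection at discharge following a negative admission screening", expressed per 1,000 patient-days.
- **Inclusion and exclusion criteria:** neither list mentions ESBL-E carriage at admission, so carriers are enrolled.
- **Statistical methods:** the count model is fitted "with log(patient-days) included as an offset". The rate difference is tested against an absolute margin of 1 per 1,000 patient-days.
- **Handling of missing data:** patients without a discharge screen are left out of the primary analysis. No other analysis exclusion is named.
- **Sample size:** the planning rate and the margin are both 1 per 1,000 patient-days; for the margin the words are "The non-inferiority margin was set at 1 additional acquisition per 1,000 patient-days". The unadjusted size is then given: "Using a one-sided alpha of 5% and 80% power, a total of 6,178 patient-days were required". A design effect of 1.48 raises this to 9,130 patient-days. The conversion to patients reads "Based on an average length of stay exceeding four days, a total of 954 patients will be included", and the allowance for losses is described as "accounting for an anticipated 15% exclusion rate".
- **Background and rationale:** a study in eight French hospitals is cited "with 28.2% of geriatric inpatients colonized".

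**The concern.** A patient already colonised at admission cannot meet the outcome definition, so that patient's days are not time at risk. The numerator is confined to admission-negative patients. Nothing in the article confines the denominator in the same way.

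One of two consequences follows:

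- **Carriers' days stay in the offset.** Both rates and their difference are diluted while the margin stays fixed. In a non-inferiority comparison this pulls the result towards the conclusion that the trial hopes to reach.
- **Carriers' days are taken out.** The 954 patients supply fewer usable days than the target, because the conversion from days to patients makes no allowance for carriage.

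That conversion also cannot be checked from the text, because the mean stay that it uses is not given.

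**Working it through.** **Inputs from the article:** CP rate 1 per 1,000; margin 1 per 1,000; one-sided alpha 5%; power 80%; 6,178 patient-days; design effect 1.48; 9,130 patient-days; 15% exclusions; 954 patients.

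**Assumptions:** carriage at admission of 10%, 20% or 28.2%. The last is the cited background prevalence in geriatric inpatients, not an admission rate for these wards. Carriers and non-carriers are taken to stay equally long.

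**Step 1. Reproduce the patient-days.** (1.645 + 0.842)² × 0.001 / 0.001² = 6,183, against the stated 6,178. This formula carries the variance of one group only; I call it the plan's own convention below. Then 6,178 × 1.48 = 9,143, against the stated 9,130, a difference of under 0.2%.

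**Step 2. Find the stay behind 954.** 9,130 / 11 = 830 exactly, and 830 × 1.15 = 954.5. An 11-day mean with the allowance multiplied on therefore reproduces the figure. If the allowance was instead divided out, 954 × 0.85 = 811 patients and 9,130 / 811 = 11.26 days. The implied mean is 11.0 to 11.3 days if no carriers are allowed for.

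**Step 3. Apply the loss.** At 11 days and 15% loss, 954 × 0.85 × 11 = 8,920 patient-days. Dividing out the loss gives 830 / 0.85 = 977 patients. This discrepancy alone is small: 8,920 is 2.3% below 9,130.

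**Step 4. Carriers' days left in the offset.** Both rates and their difference are multiplied by (1 - c), where c is carriage. The true at-risk difference that reads as 1 per 1,000 is 1 / (1 - c).

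**Step 5. Carriers' days removed.** At-risk days = 8,920 × (1 - c). Power on the plan's own convention, with the rate and margin taken per at-risk day, is Φ(0.001 / √(0.001 / (days / 1.48)) - 1.645). At 9,130 days this returns 79.9%, which matches the planned 80%; at 8,920 days it returns 79%.

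| Assumed carriage | Margin per 1,000 at-risk days if carriers stay in | At-risk days from 954 patients | Power if carriers are removed | Patients needed for 9,130 at-risk days at 11 days (×1.15 to /0.85) |
|---|---|---|---|---|
| 10% | 1.11 | 8,030 | 75% | 1,061 to 1,085 |
| 20% | 1.25 | 7,140 | 71% | 1,193 to 1,221 |
| 28.2% | 1.39 | 6,400 | 67% | 1,329 to 1,360 |

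Worked example at 28.2%: 8,920 × 0.718 = 6,404 days; 6,404 / 1.48 = 4,327; √4.327 = 2.080; 2.080 - 1.645 = 0.435; Φ(0.435) = 0.67.

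**The case against.** **No passage says that carriers' days are counted.** A reader might infer that they are. The outcome definition is compatible with an at-risk denominator, and the full protocol or analysis plan may specify one. This stands, and the point is therefore put as days not removed. It does not dispose of the matter: the article fixes the outcome, the offset and one analysis exclusion, and followed literally these put numerator and denominator on different populations.

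**28.2% is not a design input.** It is inpatient prevalence elsewhere and may include carriage acquired in hospital. This stands, hence the range. For the same reason, the 15% exclusion rate lying below 28.2% is not a contradiction, since carriage is not an exclusion criterion. What remains is that no allowance for carriers is described.

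**954 might be thought to contradict a four-day stay.** It does not. The text gives only a lower limit on the mean, and 11 days exceeds it. A mean of 15.3 to 15.7 days would even absorb 28.2% carriage, although the exact match of 830 × 11 would then be coincidence. The defect is that the figure is not stated.

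**A much larger loss of power might be blamed on carriage.** With a two-group variance, 6,400 days give about 27%. The same method gives about 34% at the full 9,130 days with no carriers at all. Most of that shortfall comes from the single-group variance behind 6,178, which is a separate matter.

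**The margin may have been meant per total patient-day.** The sources for the rate and margin are not at hand. If both were expressed over all patient-days, planning and analysis would agree and the dilution in step 4 would not apply. The article should say which is meant.

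**Conclusion.** The concern holds in this form: the event is limited to admission-negative patients, but neither the offset nor the 9,130-day target is, and the step to 954 patients shows no allowance for carriers.

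The size depends on carriage at admission, which the article does not give. Over 10% to 28.2%, leaving carriers in makes the margin equivalent to 1.11 to 1.39 per 1,000 at-risk days, provided that it was meant per at-risk day. Taking them out leaves about 8,030 to 6,400 at-risk days and power of about 75% to 67% on the plan's own convention. These are alternative consequences and do not add together. The at-risk days and power also rest on the inferred 11-day mean, on the full 15% being lost, and on equal stays in carriers and non-carriers.

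**What to change.** 1. In the primary outcome and statistical methods sections, state that numerator and offset both include only patients with a negative admission swab and a known discharge result, using those patients' patient-days.
2. State whether the assumed rate and the margin are per at-risk patient-day or per total patient-day.
3. In the sample size section, give the mean stay used, divide by (1 - loss) instead of multiplying by 1.15, add an assumed carriage at admission with a range, and restate the at-risk patient-days and power that 954 patients provide.

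The cost is a few sentences and a less favourable stated power. Both swabs are already scheduled, so no new data are needed, and the change can be made while the study is still running. If the full protocol or analysis plan already restricts the denominator, one sentence settles item 1; items 2 and 3 remain.

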### Participant timeline

The participant timeline is detailed in Table 2.

**Table 2 pone.0353783.t002:** Participant timeline.

Study phase	Admission (≤48h after admission)	During hospitalisation	At discharge
Eligibility assessment	**X**		
Written informed consent	**X**		
Baseline rectal screening for ESBL-E carriage	**X**		
Routine clinical microbiology (if clinically indicated)		**X**	**X**
Documentation of antibiotic exposure		**X**	**X**
Monitoring of clinical status and adverse events		**X**	**X**
Discharge rectal screening for ESBL-E carriage			**X**
Assessment of ESBL-E acquisition (primary outcome)			**X**

### Microbiological samples

Rectal swabs for ESBL-E surveillance cultures are obtained by trained ward nurses within 48 hours of admission and at discharge. Samples are processed in local microbiology laboratories following standardized procedures, including direct plating on chromogenic agar for ESBL-E detection. Antimicrobial susceptibility testing is performed using disk diffusion and interpreted according to CASFM–EUCAST guidelines.

All ESBL-E isolates are stored and sent to the Infection Control Department of Besançon University Hospital for molecular typing using pulsed-field gel electrophoresis. Laboratory staff performing molecular analyses are blinded to study period and IPC strategy.

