## Abstract

**Introduction:**

Extended-spectrum β-lactamase–producing Enterobacterales (ESBL-E) pose a major global public health challenge, as they are associated with frequent empirical antibiotic treatment failure and increased patient morbidity and mortality. In this context, contact precautions (CP) have traditionally been recommended for hospitalized patients colonized or infected with ESBL-E to prevent healthcare-associated transmission. However, growing evidence has questioned the effectiveness of this strategy in certain care settings.

The primary objective of this study is to assess the non-inferiority of standard precautions (SP) compared with **clinically triggered** CP in reducing the incidence density of ESBL-E acquisition in acute-care geriatric wards. By doing so, this study aims to inform the evaluation of pragmatic infection prevention policies implemented at the institutional level in vulnerable hospital populations.

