### Study objectives and hypotheses

The primary objective of this study is to assess whether SP alone are non-inferior to clinically triggered CP with respect to limiting cross-transmission of ESBL-producing Enterobacterales in acute geriatric care units.

We hypothesize that discontinuation of CP will not result in a clinically relevant increase in hospital-acquired ESBL-E. Given that the main reservoir of ESBL-E is the gastrointestinal tract, key preventive measures focus on safe handling of excreta and appropriate hand hygiene, which are core components of SP.

The secondary objective is to assess whether transmissibility differs by ESBL-E species, with the hypothesis that cross-transmission is lower for ESBL-producing Escherichia coli than for non-E. coli Enterobacterales.

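### The species-specific acquisition rates do not measure the species difference in transmissibility that the secondary objective asks about, and they can point the wrong way

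*Protocol article*

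**What the plan says.** Study objectives and hypotheses: the species question is put as "The secondary objective is to assess whether transmissibility differs by ESBL-E species". The direction that the investigators expect is then given in the same sentence: "with the hypothesis that cross-transmission is lower for ESBL-producing Escherichia coli than for non-E. coli Enterobacterales".

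Secondary outcomes: two quantities are listed. One is the "species-specific incidence density of hospital-acquired ESBL-producing" *E. coli*; the other is the same measure for Enterobacterales other than *E. coli*. Neither mentions carriers of the species.

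Primary outcome: acquisition is "defined as ESBL-E detection at discharge following a negative admission screening", expressed per 1,000 patient-days. I read the species outcomes as using the same definition and denominator.

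Microbiological samples: every ESBL-E isolate is stored and sent "for molecular typing using pulsed-field gel electrophoresis", with the typing staff blinded to period and strategy. No primary, secondary or exploratory outcome refers to the typing result.

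Statistical methods: the count model for the primary comparison uses patient-days as offset, with terms for strategy, calendar period or season, and period order. Antibiotic exposure is added in further adjusted analyses. No term represents the number of carriers on the ward, although the Background names colonization pressure as a risk factor.

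**The concern.** Transmissibility is a property of a carrier: how many new acquisitions arise per unit of time that a carrier of a given species spends on the ward. Acquisitions per patient-day multiply that property by the number of such carriers present. Two species that spread equally well will show different incidences if one is carried more often.

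The Background describes a growing burden of ESBL-producing *E. coli*, so an unequal mix of carriers is plausible here. If *E. coli* carriers predominate, *E. coli* acquisitions may be the more numerous even though each *E. coli* carrier transmits less. The study could then report evidence against its own hypothesis, or claim a species difference in transmissibility that is only a difference in prevalence. Decisions on whether precautions should differ by species could rest on that result.

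**Working it through.** **Inputs.** From the protocol: 1 acquisition per 1,000 patient-days and 9,130 patient-days (Sample size). Assumed, because the protocol gives neither: the share *s* of source carriers who carry *E. coli*, taken from 50% to 90%, and a per-carrier transmissibility ratio (*E. coli* over other species) of 0.5, which is in the hypothesised direction. The protocol states no species-specific figure, so there is none to reproduce.

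**Step 1: incidence ratio.** Suppose acquisitions come from carriers on the ward, length of stay does not differ by species, and both rates use the same patient-days. Then

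incidence ratio = per-carrier ratio × *s* / (1 − *s*).

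| *E. coli* share of carriers | *s*/(1 − *s*) | Incidence ratio, equal transmissibility | Incidence ratio, *E. coli* half as transmissible |
|---|---|---|---|
| 90% | 9.0 | 9.0 | 4.5 |
| 80% | 4.0 | 4.0 | 2.0 |
| 70% | 2.33 | 2.33 | 1.17 |
| 60% | 1.5 | 1.5 | 0.75 |
| 50% | 1.0 | 1.0 | 0.5 |

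The true per-carrier ratio is 0.5 in every row of the last column. The incidence ratio passes 1 when *s*/(1 − *s*) = 2, that is at *s* = 2/3. Above that share the outcome contradicts a true hypothesis. The incidence ratio equals the per-carrier ratio only when the two groups of carriers are equally common.

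**Step 2: does a carrier denominator repair it?** Dividing each species' acquisitions by its own carrier-days multiplies the incidence ratio by (1 − *s*)/*s*. At 80%: 2.0 × 0.2/0.8 = 0.5. At 90%: 4.5 × 0.1/0.9 = 0.5. The per-carrier ratio is recovered under the assumptions of Step 1.

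**Step 3: how much information is there?** Expected acquisitions are 9,130 × 1/1,000 = 9.13. With *s* = 80% and a per-carrier ratio of 0.5, they split 2 to 1: about 6.1 *E. coli* and 3.0 others. Treating the counts as Poisson and the carrier-days as known, the standard error of the log ratio is √(1/6.1 + 1/3.0) ≈ 0.70. The 95% factor is exp(1.96 × 0.70) ≈ 4, so an estimate of 0.5 would carry an interval of roughly 0.13 to 2.0. Clustering would widen it.

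**Step 4: the primary objective.** The Abstract words it as non-inferiority "in reducing the incidence density of ESBL-E acquisition in acute-care geriatric wards", which the primary outcome measures directly. Study objectives and hypotheses words it "with respect to limiting cross-transmission of ESBL-producing Enterobacterales in acute geriatric care units", but the hypothesis that follows there speaks of hospital-acquired ESBL-E. Under the cross-transmission wording, the outcome is a non-specific proxy: it also counts carriage missed at admission and carriage that emerges under antibiotics.

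**The case against.** A reader might infer that neither objective is measured, because both are worded as transmission and the typing has no stated use. The document does not support that for the primary. Its Abstract and its own hypothesis state the target as hospital acquisition, and the outcome and the model address exactly that. Acquisitions that do not arise from transmission cancel in the SP − CP rate difference if equally frequent in both periods. They then add only variance, which makes non-inferiority harder to show. Their size cannot be fixed from the document: it depends on swab sensitivity, which is not given, and on carriage at admission, for which the only figure (28.2%) is a prevalence among geriatric inpatients elsewhere. Antibiotic pressure is addressed in the adjusted analyses, and the Limitations concede that the source of acquisition can only be approximated.

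Nor is the lack of a described typing analysis a defect in itself. An article may leave it to a full protocol or analysis plan that is not shown.

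It is also fair to say that a carrier-based measure has weaknesses. Only enrolled carriers are seen, so patients without consent, those with stays under four days and those who die drop out. Patients who acquire carriage during the stay are not in an admission-positive denominator. Unless the numerator is restricted by typing, it still includes acquisitions that were not transmitted.

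All of this stands, and it confines the point to the secondary objective. It does not remove the point there: the species outcomes are fixed in this document and measure something other than what the objective asks.

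**Conclusion.** The secondary outcomes do not answer the secondary objective as worded. With *E. coli* half as transmissible per carrier, the planned comparison could show anything from a 4.5-fold excess to a halving of *E. coli* incidence, depending only on whether *E. coli* is 90% or 50% of carriers. Those shares and the ratio of 0.5 are assumptions. The dependence on the carrier mix does not rest on them; how far it misleads here does. The primary comparison is unaffected, apart from loose wording that the Abstract and the objectives section should share. With about 9 acquisitions expected, even a well-chosen species measure will be imprecise, so the species result should be treated as supportive.

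**What to change.** Before species-level results are examined, amend the plan in one of two ways.

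1. Keep the transmissibility objective and change its measure. Relate acquisitions of each species to patient-days of admission-positive carriers of the same species in the same unit and period, and compare *E. coli* with non-*E. coli* by the ratio of those two rates, with its confidence interval. As a supportive analysis, restrict the numerator to acquisitions whose typing pattern matches a same-species isolate from a patient in the same unit with an overlapping or preceding stay. Report this descriptively, without the margin of 1 per 1,000 patient-days, which was set for all acquisitions. The species-specific incidence densities can stay as descriptive results.

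2. Otherwise, reword the secondary objective and hypothesis as species-specific acquisition incidence, and draw no conclusion about transmissibility.

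In either case, give the primary objective the same wording in the Abstract and the objectives section, and state that acquisition is a proxy where cross-transmission is mentioned.

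The cost is extra analysis: admission swabs, species, stays and typing are already collected. The drawback is that carriers who are not enrolled are unseen, so carrier-days and linked events are both undercounted. With few events, the ratio will have a wide interval.
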